### Participants

#### Inclusion criteria

Participants with dizziness or vertigo meeting the WHO criteria (21) and international Bárány association standards (18) for PCIS will be included. Symptoms may include ataxia, unilateral or bilateral visual, motor or sensory disturbances, double vision, dysarthria or swallowing impairment. Patients must present with TCD or magnetic resonance imaging (MRI) results indicative of vertebrobasilar insufficiency.

Additionally, participants must meet all of the following criteria: 1) in the non-acute stage (defined as >14 days after stroke onset per international stroke guidelines) with stable condition and no acute exacerbation; 2) aged 30 to 80 years, both sexes; 3) dizziness or instability symptoms lasting ≥ 1 week and occurring ≥ 2 times; 4) vertigo attributable solely to central vestibular dysfunction caused by posterior circulation infarction, with no otogenic, ophthalmogenic, or other systemic causes; 5) Basel Scale Index rating scale score of more than 40; 6) able to complete or assist in completing a dizziness diary; 6) willing to cooperate with the study and sign an informed consent form.

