Pathophysiologically, normal brain function relies on stable metabolic processes, and stroke-induced cerebral metabolic imbalances and secondary structural changes (14). In clinical practice, post-stroke vertigo patients often experience dizziness that is not related to positional changes but rather to prolonged physical activity or sustained attention, associated with cerebral blood flow dysregulation and subsequent oxygen and glucose imbalance (15). Moreover, following ischemic strokes, structural changes in the brain, such as alterations in white matter integrity and gray matter volume, have been well-documented. Studies indicate that structural abnormalities, including infarct location and total lesion volume, may be closely linked to the occurrence of vertigo after stroke (16). In particular, lesions involving the vestibular nuclei, brainstem, cerebellum, or vestibulo-cerebellar structures may be especially relevant to dizziness symptoms (17). Nevertheless, in patients with PCIS, the severity and persistence of dizziness may not be fully explained by lesion topography alone. Residual vertebrobasilar hypoperfusion, altered neurovascular regulation, and secondary reorganization of vestibular-related brain regions may also contribute to symptom burden during recovery (18). Therefore, in the present trial, lesion location will be documented at baseline, while TCD, sMRI, and ASL-MRI will be used as complementary tools to characterize dynamic cerebral hemodynamics, regional perfusion, and structural changes associated with symptom persistence and recovery.

Hence, this study designed as a multicenter, large-sample randomized controlled trial aimed at: (1) Primary objective: To evaluate the specific efficacy and safety of manual acupuncture for PCIS with vertigo or dizziness by comparison with sham acupuncture. (2) Secondary objective: To compare the effectiveness and safety of manual acupuncture with western medication (betahistine) for PCIS with vertigo or dizziness. (3) Mechanistic objective: To test the *a priori* hypothesis that acupuncture alleviates vertigo by improving posterior circulation hemodynamics and regional cerebral perfusion in vestibular-related brain regions. Changes in TCD parameters, ASL-MRI perfusion, and sMRI structural markers will be evaluated and correlated with improvements in DHI scores.

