### Randomization and blinding

A random number will be generated with the R software (V.4.3.3) and concealed in opaque random envelopes. The envelopes will be prepared by a third party in advance, with the sequence number labeled on the surface and the random number and group allocation information sealed in. The random envelopes will be preserved by special personnel who are not involved in treatment and evaluation. Participants are randomly assigned in a ratio of 1:1:1 to manual acupuncture (MA) group, sham acupuncture (SA) group, and western medication (WM) group.

Given the use of two distinct acupuncture techniques in this trial, the acupuncturist will be aware of the group allocation for each participant. However, identical auxiliary devices will be used in both the acupuncture and sham acupuncture groups to maintain blinding for participants. Participants in both groups will remain unaware of their specific group assignment. Furthermore, outcome assessors and statisticians will be blinded to group allocations throughout the study to minimize bias. To maintain blinding, all researchers will undergo identical training prior to the trial, and treatments will be administered in separate rooms for each participant. It should be noted that participants in the medication group will not be blinded.

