#### Exclusion criteria

Patients who meet any of the following conditions will be excluded: 1) dizziness confirmed to be caused by other diseases or trauma; 2) history of central nervous system disorders (e.g., cerebral hemorrhage, intracranial infection) within the past 6 months; 3) severe underlying primary diseases affecting the cardiovascular, respiratory, hepatic, renal, hematopoietic systems, or serious dysphrenia; 4) severe skin infections at acupuncture point; 5) pregnant or lactating women; 6) currently participating in another clinical trial or having participated in one within 3 months prior to recruitment.

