### Treatment expectations assessment

Before the treatment, participants in each group will be asked, “How do you perceive the final efficacy of the treatment?” Participants will select from one of five options: 1) highly effective (symptom improvement >75%); 2) moderately effective (symptom improvement 50%–75%); 3) slightly effective (symptom improvement 25%–50%); 4) no change (symptom improvement 0–25%). Responses indicating “highly effective” will be categorized as high expectations, while all other responses will be categorized as low expectations.

To minimize expectation bias, outcome assessors and statisticians will remain fully blinded to group allocation throughout the study. In addition, treatment expectation level will be incorporated as a covariate in the statistical analysis of the primary outcome (DHI) to adjust for its potential confounding influence on subjective symptom reports. To further ensure objectivity, all assessments will be performed using standardized procedures, and expectation evaluation will be conducted by a researcher blinded to treatment assignment.

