### Statistical analysis

Analyses for this study will be conducted in accordance with both the intention-to-treat (ITT) principle and the per-protocol set (PPS) approach. The ITT analysis will include all randomized participants, and the missing data will be imputed using the Last Observation Carried Forward (LOCF) method, with the most recent observed data carried forward for filling. The PPS will include participants who have completed at least 80% of the prescribed treatment. SPSS 23.0 software will be used for statistical analysis. Quantitative indicators are described using mean, standard deviation, median, 25th percentile and 75th percentile. Categorical indicators are described using frequencies and percentages.

To control the Type I error caused by multiple comparisons, the Bonferroni correction will be adopted for pairwise comparisons of the primary outcome (DHI total score) among the three groups (manual acupuncture vs. sham acupuncture, manual acupuncture vs. western medication, sham acupuncture vs. western medication), with the adjusted significance level set at *p* < 0.017 (0.05/3); for secondary outcomes (DARS scores, dizziness diary indicators including attack frequency, duration and severity), the false discovery rate (FDR) method will be used for multiple comparison correction to balance the Type I and Type II error rates in exploratory analysis of multiple secondary indicators.

Since this study is a multicenter clinical trial, sub-center and corresponding baseline values were incorporated as covariates in the generalized linear model for analysis. Additionally, binary logistic regression was employed to analyze the impact of high versus low expectations on the primary efficacy endpoint across groups. The dependent variable in this analysis was response status, defined as participants showing at least a 50% reduction in total DHI scale score from baseline after 3 weeks of treatment (referred to as responders). The independent variable was the level of expectation (high or low).

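### Exclusion 2 does not exempt the index infarct and so conflicts with the 14-day entry rule; time since onset and lesion location are absent from the stated covariates

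*Protocol article*

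**What the plan says.** **Eligibility.** Under Inclusion criteria, item 1 requires patients to be "in the non-acute stage (defined as >14 days after stroke onset per international stroke guidelines) with stable condition and no acute exacerbation". No upper limit on time since stroke is given. Item 4 requires "vertigo attributable solely to central vestibular dysfunction caused by posterior circulation infarction", so every participant has had an infarct of the central nervous system. Under Exclusion criteria, item 2 removes patients with a "history of central nervous system disorders (e.g., cerebral hemorrhage, intracranial infection) within the past 6 months".

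**Rationale.** The Introduction names lesions of the vestibular nuclei, brainstem and cerebellum as possibly of particular relevance to dizziness. It adds that "secondary reorganization of vestibular-related brain regions may also contribute to symptom burden during recovery", and states that "lesion location will be documented at baseline". Its mechanistic objective is to correlate changes in the transcranial Doppler (TCD), perfusion (ASL-MRI) and structural (sMRI) measures with DHI improvement.

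**Allocation and analysis.** Randomization and blinding says "Participants are randomly assigned in a ratio of 1:1:1" and names no stratification factor. Statistical analysis says "sub-center and corresponding baseline values were incorporated as covariates in the generalized linear model for analysis". Treatment expectations assessment adds expectation level as a covariate for the DHI. Neither time since onset nor lesion location appears in any stated analysis.

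**The concern.** There are two linked problems.

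First, a patient 15 days to 6 months after the index infarct is admitted by inclusion 1 and, on the literal wording, removed by exclusion 2. A centre that follows the letter would recruit only strokes older than 6 months. A centre that reads the clause as covering other disorders would recruit from day 15. The trial population would then depend on who reads the criteria.

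Second, the protocol's argument for measuring perfusion and structure is that these change during recovery and bear on symptoms. If so, where a patient stands in recovery, and where the lesion lies, may predict the change in both DHI and the imaging markers whatever the allocated treatment. For the randomised contrast, leaving such factors out costs some precision. For the correlation between imaging change and DHI change it is more serious. A patient who is recovering spontaneously may show both, and the association could be read as support for the acupuncture mechanism.

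**Working it through.** **1. The eligibility text, side by side**

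| Time since index infarct | Inclusion 1 | Exclusion 2, literal | Exclusion 2, read as other disorders |
|---|---|---|---|
| Up to 14 days | not eligible | excluded | not excluded |
| Day 15 to 6 months | eligible | **excluded** | **not excluded** |
| Over 6 months | eligible | not excluded | not excluded |

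The readings differ in effect only in the middle row. On the literal reading the 14-day limit never decides a case, because everyone it would admit before 6 months is removed anyway. Two features favour the narrower reading: the 14-day limit would otherwise be pointless, and both examples are conditions different from the index disease. One feature counts against relying on that: exclusion 1 in the same list explicitly says *other* diseases, and exclusion 2 does not.

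**2. The plan's sample size (to see whether this point touches it)**

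Inputs from Sample size calculation: means 21 (manual), 33 (sham) and 30 (betahistine), SD 20, two-sided 0.05, power 90%, dropout 15%.

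- Grand mean 28; squared deviations 49 + 25 + 4 = 78.
- Noncentrality at 66 per group: 66 × 78 / 20² = 12.87. The one-way ANOVA F-test then has power 0.9005.
- 66 / 0.85 = 77.6, hence 78 per group and 234 in total.

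The stated figures reproduce exactly.

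**3. Precision gain for the manual-versus-sham DHI contrast**

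The documents give no data on how much DHI variance these factors explain. Assume R² of 5–15% of the residual variance. Interval narrowing is 1 − √(1 − R²); the equivalent gain in patients per arm is 66/(1 − R²) − 66.

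| R² (assumed) | Interval narrower by | Worth, patients per arm |
|---|---|---|
| 0.05 | 2.5% | 3.5 |
| 0.10 | 5.1% | 7.3 |
| 0.15 | 7.8% | 11.6 |

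**4. Chance imbalance in the same contrast**

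Assume half the patients are early-stage and that they improve 10 DHI points more than the rest.

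- SE of the difference in proportion early-stage, 78 per arm: √(2 × 0.5 × 0.5 / 78) = 0.080.
- Probability of an imbalance of 10 percentage points or more: z = 0.10/0.080 = 1.25, two-sided about 0.21.
- Shift at the 95% limit of imbalance: 1.96 × 0.080 × 10 = 1.6 points.
- For scale: the planned difference is 12 points, and the SE of the contrast is 20 × √(2/66) = 3.5 points.

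**5. The imaging–DHI correlation**

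If a common cause explains a share R² of each of two changes, and there is no other link between them, it induces a correlation of √R² × √R² = R². Carrying over the assumed 5–15% to both DHI change and an imaging change gives a correlation of 0.05–0.15 with no mechanism at all. With 198 patients pooled, the Fisher z statistic is atanh(r) × √195: 0.05 × 13.96 = 0.7 at the low end and 0.151 × 13.96 = 2.1 at the high end. Unlike the chance imbalance in step 4, this does not shrink as the sample grows.

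**The case against.** The case against is substantial.

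- **The literal reading is strained.** The examples point to other disorders, a neurology specialist decides eligibility, and SOPs and common training are planned. That makes divergence less likely, but the criterion still permits both readings. Any stage difference between centres in mean DHI would be absorbed by the centre covariate. That covariate does not settle which population the trial studies, and it does not adjust for stage within a centre.
- **Broad eligibility is legitimate.** The absence of an upper time limit is a design choice, and stable condition is required. This stands.
- **The rationale is hedged.** The Introduction says these processes may contribute and that lesion site may not fully explain symptoms. It never states an expected course by time since stroke. This stands too: the factors are plausible, not proven, predictors.
- **Covariates may sit in an analysis plan that is not shown.** The stated list is not declared exhaustive, and a supportive subgroup table is ordinary analysis-plan material, so its absence is not a fault. But the article does name covariates for the primary analysis, and the two that its own rationale suggests are not among them.

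A reader might infer that unadjusted recovery stage biases the primary comparison. The documents do not support that. Manual and sham arms are concurrent and randomised, baseline DHI is in the model, and chance imbalance in a prognostic factor is already allowed for in the confidence interval and the type I error.

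A reader might also infer that the trial is underpowered because of mixed recovery stages. That does not follow either: the planned SD of 20 may already include this variation, in which case nothing is lost.

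**Conclusion.** The eligibility conflict is textual and rests on no assumption: the 14-day entry rule and exclusion 2 must be reconciled. The likely intention can be guessed, but the wording should not leave it to be guessed at three centres.

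The covariate point holds in a limited form. For the manual-versus-sham DHI contrast it offers a modest gain in precision, about 2.5–8% on the interval under an assumed R² of 5–15%. It does not remove a systematic bias. The illustrative shift of 1.6 points is an extreme of chance under assumed inputs and is small beside the planned 12. The inputs are also only loosely compatible: a 10-point gap at an even split contributes a variance of (10/2)² = 25, or 6% of 400, so 15% would require a gap of about 15 points.

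The better reason to adjust is the correlation of imaging change with DHI improvement. It is not a randomised comparison, and spontaneous recovery is an obvious common cause. The size there is equally unknown, and the 0.05–0.15 range only carries the same assumption across. The sample size of 66, then 78 per group, stands.

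**What to change.** 1. State explicitly in the eligibility text whether the index posterior circulation infarct falls under exclusion 2, so that it and inclusion 1 give one answer between day 15 and 6 months. Which population is intended is for the sponsor to decide. Brief all three centres on the clarified text, and check how patients already screened were handled.
2. Record the stroke onset date on the case report form. The study schedule lists disease history but not this date, and inclusion 1 needs only confirmation that 14 days have passed.
3. Prespecify time since onset (log-transformed, since its range is wide) and baseline lesion location (vestibular nuclei, brainstem or cerebellum versus other) as covariates in the DHI model and in the TCD, ASL-MRI and sMRI group comparisons.
4. Above all, include both, together with treatment arm, in the analysis relating imaging change to DHI improvement, and report that association as observational.

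Cost: one clarified line, one recorded date and a few degrees of freedom. Lesion location is already to be documented. No extra visits, scans or patients are needed. Fixing the covariates before unblinding also rules out a later, data-driven choice to adjust.

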#### Exclusion criteria

Patients who meet any of the following conditions will be excluded: 1) dizziness confirmed to be caused by other diseases or trauma; 2) history of central nervous system disorders (e.g., cerebral hemorrhage, intracranial infection) within the past 6 months; 3) severe underlying primary diseases affecting the cardiovascular, respiratory, hepatic, renal, hematopoietic systems, or serious dysphrenia; 4) severe skin infections at acupuncture point; 5) pregnant or lactating women; 6) currently participating in another clinical trial or having participated in one within 3 months prior to recruitment.

### Patient recruitment

Recruitment strategies include poster, online platforms, and rehabilitation and neurology departments inpatients. Potential patients will be informed about the study specifics, including the purpose, subgroup allocation, interventions, treatment period, benefits, and potential risks. A neurology specialist will assess and diagnose interested patients to determine their eligibility. Eligible individuals who voluntarily choose to participate will be required to sign a written informed consent form prior to the start of the study. All patient information will be kept confidential. Participants have the right to withdraw from the study at any stage, with reasons for withdrawal being thoroughly documented.

### Intervention and comparison

All patients will receive guideline-based interventions (22, 23) for the secondary prevention of ischemic stroke which include: 1) management of risk factors such as blood pressure and blood glucose; 2) targeted treatments: administration of aspirin for antiplatelet therapy or warfarin for anticoagulation, as appropriate, along with atorvastatin for lipid regulation and plaque stabilization; 3) patient education on dietary and lifestyle modifications. Specific interventions for each group are as follows: the MA group will receive manual acupuncture in addition to standard secondary prevention treatment; the SA group will receive sham acupuncture alongside standard secondary prevention treatment; and the WM group will receive betahistine (24) in conjunction with standard secondary prevention treatment.

### Manual acupuncture (MA) group

The selected acupuncture points—Baihui (DU20), Fengchi (GB20), Wangu (GB12), and Taichong (LR3)—were determined based on preliminary literature review and consensus among acupuncture experts for this study. Detailed descriptions of each acupoint are provided in Table 2 and illustrated in Figure 2. All acupuncturists are licensed and have a minimum of 3 years of clinical experience. Prior to the trial, all acupuncturists will undergo training on acupoint positioning and manipulation techniques. Each sub-center will be assigned one acupuncturist who will be responsible for treating all patients at that center.

**Table 2 tab2:** Locations of acupoints.

Acupoints	Locations
Baihui (DU20)	On the median line of the head, 5 inches superior to the anterior hairline, at approximately the middle of the connecting line between the two auricular tips.
Fengchi (GB20)	On the posterior neck, inferior to the occipital bone, in the depression between the origins of sternocleidomastoid and the trapezius muscles.
Wangu (GB12)	On the posterior aspect of the head, in the depression between the mastoid process and the inferior nuchal line of the occipital bone.
Taichong (LR3)	0.5 to 0.8 finger breadths laterally to the dorsum of the foot, in the distal depression of the angle proximal between the 1st and 2nd metatarsa.

**Figure 2 fig2:**
[figure not shown]
Location of real acupoints and sham acupoints **(A,B)**. DU, Du Mai; GB, Gallbladder Meridian; LR, Liver Meridian; TE, Triple Energizer Meridian.

During the acupuncture process, patients will maintain a semi-recumbent position. The acupuncturist will sterilize the skin around the acupoint using 75% alcohol, then stick a foam base to the acupoint and insert the needle through the foam base (Figure 3A). For DU20, a 1 cun needle (0.30 × 25 mm, Suzhou Hua Tuo, China) will be inserted laterally to a depth of approximately 0.5–0.8 cun at a 15° angle relative to the skin. For GB20, GB12, and LR3, needles of the 1 cun (0.30 × 25 mm, Suzhou Hua Tuo, China) will be inserted to a depth of approximately 0.5–1.0 cun. Needles will be retained for 30 min, with manipulation (lifting, thrusting, twisting, and rotating) performed every 10 min to achieve the sensation of “De Qi.” Upon needle removal, a dry-sterilized cotton ball will be used to gently press the needled area to prevent bleeding. Each patient will undergo a 3-week acupuncture treatment regimen, receiving five sessions per week for a total of 15 sessions.

**Figure 3 fig3:**
[figure not shown]
Illustration of acupuncture. **(A)** Real acupuncture device; **(B)** Sham acupuncture device; **(C)** Usage of device.

### Sham acupuncture (SA) group

The sham acupuncture procedure closely mirrors that of manual acupuncture. The procedure will be also performed using Streitberger placebo needles which will be applied at non-acupoint locations, approximately 1–1.5 cun lateral to the actual acupoints along the meridians (Figure 2 and Figure 3B). No lifting, thrusting, or rotating manipulations will be performed, and no “De Qi” sensation will be elicited. The patients may experience a sensation of pain but not skin puncture. To address ethical considerations, participants in the sham acupuncture group will receive a free compensatory acupuncture treatment at the conclusion of the trial. After randomization, participants receive treatment five sessions per week for 15 sessions for three consecutive weeks.

